## Abstract

**Background:**

Arthritis and musculoskeletal conditions are the leading cause of long-term work disability (WD), an outcome with a major impact on quality of life and a high cost to society. The importance of decreased at-work productivity has also recently been recognized. Despite the importance of these problems, few interventions have been developed to reduce the impact of arthritis on employment. We have developed a novel intervention called “Making It Work”, a program to help people with inflammatory arthritis (IA) deal with employment issues, prevent WD and improve at-work productivity. After favorable results in a proof-of-concept study, we converted the program to a web-based format for broader dissemination and improved accessibility. The objectives of this study are: 1) to evaluate in a randomized controlled trial (RCT) the effectiveness of the program at preventing work cessation and improving at-work productivity; 2) to perform a cost-utility analysis of the intervention.

**Methods/Design:**

526 participants with IA will be recruited from British Columbia, Alberta, and Ontario in Canada. The intervention consists of a) 5 online group sessions; b) 5 web-based e-learning modules; c) consultations with an occupational therapist for an ergonomic work assessment and a vocational rehabilitation counselor. Questionnaires will be administered online at baseline and every 6 months to collect information about demographics, disease measures, costs, work-related risk factors for WD, quality of life, and work outcomes. Primary outcomes include at-work productivity and time to work cessation of > 6 months for any reason. Secondary outcomes include temporary work cessation, number of days missed from work per year, reduction in hours worked per week, quality adjusted life year for the cost utility analysis, and changes from baseline in employment risk factors. Analysis of Variance will evaluate the intervention’s effect on at-work productivity, and multivariable Cox regression models will estimate the risk of work cessation associated with the intervention after controlling for risk factors for WD and other important predictors imbalanced at baseline.

**Discussion:**

This program fills an important gap in arthritis health services and addresses an important and costly problem. Knowledge gained from the RCT will be useful to health care professionals, policy planners and arthritis stakeholders.

**Trial registration:**

ClinicalTrials.gov NCT01852851; registered April 13, 2012; first participant randomized on July 6, 2013.

## Background

Work disability (WD) is a common and early outcome of inflammatory arthritis (IA), with a major impact on quality of life and a high cost to those affected, their families and society [1,2]. Arthritis and musculoskeletal conditions are the leading cause of long-term WD in many countries, including Canada and the US [3,4]. Recent studies have also drawn attention to the importance of decreased productivity while at work, or presenteeism [5]. Despite the importance of the problem, there has been little research on interventions to reduce the impact of arthritis on employment [6-9]. Lack of employment services has also been identified by people living with arthritis as an important unmet need in qualitative studies [10-12]. It represents an important gap from a clinical care and a health services research perspective.

To close this care gap, we have developed and pilot tested a novel intervention targeting employed people with IA, to prevent WD and improve at-work productivity [13]. Our “Employment and Arthritis: Making It Work Program” is unique in that it combines the benefits of group sessions and self-learning modules aimed at enhancing self-management of work-related problems, and individualized assessments by employment-related health professionals, including an ergonomic assessment by an occupational therapist (OT) and job retention vocational rehabilitation counselling (VRC). Program development was based on a strong theoretical background, the self-management approach proven effective in arthritis management [14,15] and the precede-proceed model [16-18], a validated model successfully used for developing health education programs. Program content was selected to modify known risk factors for WD and problems at work identified in initial focus groups [10]. A proof of concept study of the intervention showed favourable results after 12 months of follow up [13]. The program has now been converted to a web-based format to allow broader dissemination of the program, and to address feedback from participants who found it difficult to attend sessions at the end of a work day, given the fatigue and difficulty commuting associated with their IA. This evolution is consistent with recent trends in adult learning, health education and in self-management programs [19-31].

The objectives of this study are: 1) to evaluate, in a randomized controlled trial (RCT), the effectiveness of the program at preventing work cessation and improving at-work productivity compared to a control group receiving usual care; 2) to perform a cost-utility analysis of the intervention.

## Methods/design

### Study design

Our study design is consistent with CONSORT recommendations for RCTs, 2010 update [32] and extension for trials of non-pharmacological treatments [33]. Participants will be stratified by location and arthritis type and randomized 1:1 to receive either our program, or “usual care” as initiated by their physician and supplemented by printed material about work and arthritis. Participants will be followed for 5 years, the estimated time required, according to our power calculations, to observe a difference in work cessation similar to that in Allaire’s RCT [34]. After 2 years, analysis of our first primary outcome, at-work productivity, will be performed, along with an interim analysis of the second primary outcome, work cessation. If a significant difference in work cessation is observed between the two groups, the RCT will be terminated prematurely. Because of the nature of the intervention, participants cannot be blinded. Ethics approval was obtained from the University of British Columbia Research Ethics Board (H11-03527).

### Study sample

526 participants will be recruited from British Columbia, Alberta, and Ontario. To be eligible to participate, individuals must: 1) have a physician confirmed diagnosis of IA (including rheumatoid arthritis, psoriatic arthritis, systemic lupus erythematosus, or spondyloarthropathies); 2) Be between the ages of 18 and 59 years; 3) Be able to read and write in English without the assistance of a translator; 4) Be currently employed (full time, part time, self-employed, or contract work); 5) Be at risk of job loss, defined as answering yes to: “Do you have any concern about your arthritis affecting your ability to work now, or in the next five years?”; 6) Have access to a personal computer with high-speed, wired-in internet connection and have access to, or willingness to purchase, a webcam and headset for the virtual group meetings and VRC assessments; 7) Be willing to travel for one visit with an OT.

### Randomization

Randomization will be stratified by study centre (3 levels) and type of arthritis (4 levels). In each stratum, we will use blocked randomization, with random and variable block sizes, to ensure optimal balance between trial arms, while avoiding the risk of study personnel ‘guessing’ the next allocation. Randomization will be performed centrally, in Vancouver; by the biostatistician (CG) using a customized program in the R programming language, after the study coordinator has confirmed eligibility and received informed consent. To ensure concealment of the randomization list from those making eligibility decisions, allocations will be available for one patient at a time.

### Intervention

The intervention consists of three components:

1) Five interactive web-based eLearning modules, completed individually by participants in between the biweekly group sessions. The modules cover relevant topics such as work and arthritis, management of IA, dealing with fatigue and stress at work, effective communications skills, disclosing one’s arthritis diagnosis, optimizing interpersonal relationships at work, job accommodations, and vocational counselling. In addition to providing didactic information, reflective exercises improve self-awareness and allow participants to apply the concepts learned to their own personal situation. Self-management techniques and other relevant skills are also taught and practiced.

2) Five 2-hour biweekly group sessions conducted as virtual real-time group meetings, with 10–12 participants per group, led by a facilitator with knowledge of arthritis and experience leading self-management or education programs. The group interactions allow participants to share experiences, learn from each other, practice skills, and report back to the group on the progress of their action plans. These interactions were highly valued by participants of our pilot test, who described experiencing validation by hearing from others living similar situations, benefiting from others’ experiences and solutions, receiving peer support, and being motivated to implement changes by having to report back to the group [13].

3) Consultations with an OT and a VRC. After completing the web-based modules and group meetings, participants have an in-person consultation with an OT for an ergonomic assessment of their work. The OT uses a standardized tool we developed for people with IA called the Ergonomic Assessment Tool for Arthritis (EATA) [35], to identify ergonomic problems and risks, and recommend ergonomic modifications as job accommodations. A telephone follow-up is performed one month later to discuss implementation of recommendations and help overcome barriers. A vocational counsellor provides “job retention” VRC, using a standardized guide developed for our program, with an initial consultation performed using web technology and a follow-up one month later by telephone. The assessment focuses on identifying problems at work and developing solutions, evaluating the need for job accommodations and helping in the process of requesting and obtaining job accommodations, short and long-term planning such as determining if additional training would facilitate long-term goals, as well as discussing individual issues such as the decision to disclose one’s arthritis, or dealing with interpersonal difficulties with co-workers or supervisors.

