### Sample size and analysis

Sample size was calculated for the primary outcome requiring the largest sample, i.e. time to work cessation. It was performed with PASS software [42] for time-to-event analyses. We assumed 5 years of follow-up and a rate of work cessation of 12.77% per year in the control group, based on the 40% work loss observed in controls over 4 years in Allaire’s RCT of VRC [34], and assuming an exponential distribution of time to work loss. A sample size of 420 subjects (210 per group) completing the study is necessary for 80% power, a 2-tailed Cox model-based score test, equivalent to the logrank test, at alpha = 0.05, to detect a 35% relative risk reduction (HR = 0.65) in the intervention vs. control group, which was considered a minimally clinically important difference (MCID), and is moderately conservative compared to the 42% risk reduction observed in Allaire’s study (HR = 0.58, 95% CI:0.34-0.99) [34]. Assuming 20% loss to follow-up, we will recruit a total of 526 subjects (263 per group). This sample will ensure adequate power for our other primary outcome, at-work productivity.

Appropriate descriptive statistics will be used to measure baseline characteristics of the two groups. Analysis of treatment effectiveness will rely on intention-to-treat (ITT) approach, so that all patients initially randomized will be included in the analysis, regardless of their compliance or drop-outs.

For the analysis of our first primary outcome, at-work productivity measured as a continuous variable will be tested for normality using the Shapiro-Wilk test [43]. If normality assumption is rejected, an appropriate transformation (e.g. such as logarithmic) will be employed to obtain an approximately normal distribution. Next, an Analysis of Variance (ANOVA) will evaluate the effect of the intervention on WIS measures at 2 years, adjusting for the 12 strata and blocking. We will also consider an Analysis of Covariance model after inspection of the baseline values in both treatment arms for factors such as WIS score, duration of disease, physician providing RA care, age, gender and risk factors for WD. If differences at baseline are observed, we will consider them as covariates. Since the power of these analyses will likely be less than the original ANOVA, post hoc power analyses will be conducted if these appear to be clinically meaningful adjustments.

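### The program is delivered in groups of 10–12 in one arm only, but both primary analyses and the sample size treat participants as independent; any within-group correlation makes the planned standard errors too small

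*Protocol article*

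**What the plan says.** The Study design and Randomization sections describe 1:1 individual randomization, stratified by centre and arthritis type, in blocks of varying size. The Intervention section then puts one arm into groups: "Five 2-hour biweekly group sessions conducted as virtual real-time group meetings, with 10–12 participants per group, led by a facilitator". It presents the exchange within these groups (peer learning, mutual support, reporting back on action plans) as part of how the program works. The Control group section describes printed information and usual care, with no grouping.

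Under Sample size and analysis, the first primary outcome is analysed as follows: "an Analysis of Variance (ANOVA) will evaluate the effect of the intervention on WIS measures at 2 years, adjusting for the 12 strata and blocking". The blocking here is most naturally the randomization blocks, not the session groups. The second primary outcome is compared by Kaplan-Meier curves and a logrank test, then by a Cox model with baseline covariates. The sample size rests on "a 2-tailed Cox model-based score test, equivalent to the logrank test, at alpha = 0.05", and the result is "A sample size of 420 subjects (210 per group) completing the study is necessary for 80% power". No ICC, design effect, random effect, frailty or robust variance for session group or facilitator appears, and the Limitations section does not mention clustering.

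**The concern.** This is an individually randomized trial with treatment groups in one arm, that is, a partially nested design. Members of a session group share a facilitator and influence one another, so their later outcomes may be correlated. Adjusting for strata and randomization blocks does not remove correlation that arises after randomization, in groups formed for treatment.

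If such correlation exists, the planned standard errors are too small. Confidence intervals are then too narrow and the nominal 5% level is exceeded, so a false claim of benefit becomes more likely. The stated power also omits the cost of the clustering. The Discussion section expects the results to inform decisions on funding the program, so the precision claimed for the effect matters.

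**Working it through.** **Inputs from the protocol article (Sample size and analysis; Intervention).** Control hazard: "a rate of work cessation of 12.77% per year in the control group". Effect: "to detect a 35% relative risk reduction (HR = 0.65) in the intervention vs. control group". Duration: "We assumed 5 years of follow-up". Two-sided alpha 0.05; 80% power; 420 completing; 20% loss; 526 recruited; groups of 10–12, midpoint m = 11.

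**Assumed, not in the document.** ICC of 0.01, 0.02 or 0.05, and a constant rate of loss to follow-up.

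**1. Reproduce the plan's figure.**
- Hazard: −ln(0.60)/4 = 0.1277 per year.
- Events (Schoenfeld): 4 × (1.960 + 0.842)² / (ln 0.65)² = 169.2, so 170.
- Event probability over 5 years: control 1 − exp(−5 × 0.1277) = 0.472; intervention 1 − exp(−5 × 0.1277 × 0.65) = 0.340; mean 0.406.
- N = 170/0.406 ≈ 419, so 420 in equal arms. At 420 there are 170.4 expected events and power is 80.3%.
- Recruitment: 210/0.80 = 262.5, so 263 per arm and 526 in all.

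The plan's figure is thus reproduced with no allowance for clustering.

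**2. Variance inflation with clustering in one arm.** There are about 263/11 ≈ 24 session groups. The design effect in the intervention arm is 1 + (m − 1) × ICC; in the control arm it is 1. With equal arms, the variance of the difference inflates by VIF = [1 + 1 + (m − 1) × ICC]/2 = 1 + 5 × ICC.

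**3. Type I error of the planned test, which ignores clustering:** 2 × [1 − Φ(1.96/√VIF)].

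**4. Power of a clustering-adjusted test, 420-completer basis** (calibrated to the stated 80%): Φ(2.8016/√VIF − 1.96).

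**5. Power of a clustering-adjusted test, all 526 followed to censoring.** A constant loss rate giving 20% by year 5 is −ln(0.80)/5 = 0.0446 per year. The probability of an observed event is λ/(λ + 0.0446) × [1 − exp(−5(λ + 0.0446))]: 0.428 for control and 0.307 for intervention, mean 0.367. Expected events: 526 × 0.367 ≈ 193. The expected test statistic is √193.2/2 × 0.4308 = 2.994, giving about 85% power under independence. With clustering, power is Φ(2.994/√VIF − 1.96).

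| ICC (assumed) | VIF | SE ratio | Type I error, planned test | Adjusted-test power, 420 completers | Adjusted-test power, 526 to censoring |
|---|---|---|---|---|---|
| 0 | 1.00 | 1.00 | 5.0% | 80% | 85% |
| 0.01 | 1.05 | 1.02 | 5.6% | 78% | 83% |
| 0.02 | 1.10 | 1.05 | 6.2% | 76% | 81% |
| 0.05 | 1.25 | 1.12 | 8.0% | 71% | 76% |

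On the 526 basis, power reaches 80% when VIF = (2.994/2.8016)² = 1.142, that is, at an ICC of 0.142/5 ≈ 0.03.

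**6. Sensitivity to group size.** At ICC 0.05, m = 10 to 12 gives 71.6% to 69.9% power on the completer basis. If only completers count, groups average 210/24 = 8.75; at ICC 0.05, VIF is then 1.19, type I error 7.3% and adjusted power 73%.

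**7. WIS.** The variance inflation and type I error above apply as an approximation. No power can be computed, because the article gives no standard deviation or target difference for this outcome.

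**The case against.** **The ICC is unknown and may be small.** E-learning is done alone and the occupational therapist and vocational consultations are individual. Group contact is limited to five sessions, while outcomes are read at 2 years and over 5 years, and work cessation counts all causes. This stands: the size is an assumption and must be shown as a range that includes zero.

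**Under a strict null there may be no inflation.** If the program affects nobody, the groups induce no correlation and the test stays near 5%. The type I errors above apply when group effects vary but average to zero. This also stands. A reader might infer that type I error certainly exceeds 5%; the document does not establish that.

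**There is a cushion for work cessation.** All randomized participants are analysed and those lost are censored, so 526 contribute rather than 420. A reader might infer that this trial's power is simply 71–78%. That is the completer basis only, and it belongs to a clustering-adjusted test. The inflated type I error belongs to the unadjusted test, whose probability of rejecting under the design alternative, Φ(0.8416/√VIF), is 79.4%, 78.9% and 77.4% at the three ICCs. No single test has both 8.0% type I error and 71% power. The cushion also does not correct the planned standard errors.

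**Variance estimation could be left to an analysis plan.** This does not stand in full. The article itself names both primary models, lists the ANOVA adjustment terms and states a sample size derived under independence.

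**Conclusion.** The point holds conditionally. Treatment is grouped in one arm, and the stated analyses and sample size ignore it. For any positive within-group correlation the planned standard errors are too small, by a factor of about 1.02 to 1.12 over an assumed ICC of 0.01 to 0.05.

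The effect on power for work cessation is modest at the low end. If all 526 are followed to censoring under the assumed loss pattern, 80% is lost only above an ICC of about 0.03. A reader might infer that the trial is underpowered or must recruit more; the documents do not support that, since they give no ICC and the survival analysis uses more participants than the 420 in the calculation. Equally, no cushion can be shown for WIS, where adequate power is asserted without figures.

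The figures rest on m = 11, equal arms, a normal approximation and the ICC scale carried over to the log hazard ratio. Severity: should be fixed.

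**What to change.** - Use the session-group identifier, and the facilitator identifier, in both primary analyses. The article does not say whether these are recorded; confirm that they are, since membership is hard to recover later.
- WIS at 2 years: fit a partially nested mixed model with a random group effect in the intervention arm only, controls as singletons, and arm-specific residual variance, keeping the stratification factors.
- Work cessation: use a Cox model with cluster-robust variance or a shared frailty by session group, each control forming their own cluster. Base the inference on this rather than on the unadjusted logrank test, at the interim look as well.
- Keep the sample size. State power for the adjusted test over an explicit ICC range, with the basis labelled (420 completers, or 526 to censoring with the loss assumption). For WIS, give the standard deviation and target difference before stating any power.
- Fix the wording before the 2-year analysis.

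The cost is one or two recorded variables and revised analysis text. The downside is slightly wider intervals and a less favourable stated power.

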### Control group

The control group will receive printed materials providing information about arthritis and employment available from arthritis websites and non-profit organizations. They will also receive “usual care” from their physicians and allied health professionals. Data will be collected, in follow-up assessments, on information and support received to address employment issues. To minimize loss to follow-up, all controls will be offered the intervention at study end.

### Data collection

Data will be collected on demographics, disease variables, co-morbidities, quality of life, costs, work-related risk factors for WD, and work outcomes, using a self-administered online questionnaire. Work outcomes, costs and quality of life will be assessed every 6 months, and other data once yearly. To evaluate co-interventions received in both groups, data will also be collected every 6 months about IA treatment received, “usual care” received from physicians and allied health professionals, information sought about employment issues, use of services specifically targeted at employment, and job accommodations made.

### Outcome measures

#### **
*Primary work outcomes*
**

The first primary outcome will be presenteeism, or at-work productivity, measured over 2 years, using the Work Instability Scale (WIS-RA) [36]. Developed for RA, the WIS measures mismatch between functional ability and work demands, and was designed to identify individuals at high risk of work loss warranting referral for vocational assessment. It has been shown to have good psychometric properties, including construct validity [37], and be effective at predicting future work transitions [38]. However, a drawback of the WIS is that it does not permit the calculation of associated costs. Therefore, for the purpose of the cost-utility analysis, at-work productivity will be measured using the Work Productivity and Activity Impairment – Specific Health Problem (WPAI-SHP) scale [39]. The WPAI-SHP measures overall impairment in activities (from work time missed, impairment while working, and activity impairment outside of work) due to a health problem, expressed as percent impairment, which can be used to calculate associated cost. Statistically significant improvement in both the WIS and the WPAI-SHP were observed in our pilot study.

The second primary outcome will be time to work cessation, measured over 5 years of follow up. Work cessation is defined as complete cessation of work for more than 6 months, the standard duration used by insurance companies to define permanent WD, and also consistent with definitions of WD in the employment literature [40]. This definition will capture WD from all health reasons (i.e. not only related to arthritis), including early retirement, work cessation for personal reasons, and prolonged unemployment periods when people are looking for another job, but will not capture temporary WD, sick leave, or short periods of unemployment of less than 6 months duration. Whether or not work cessation should be restricted to arthritis related work cessation is an issue of debate in the arthritis employment literature. Because of difficulties attributing work cessation to a single cause (i.e. the decision is often multifactorial and arthritis may have played some role in the decision), it is generally recommended that all-cause work cessation be measured in studies including a control group [41].

#### **
*Secondary work outcomes*
**

Secondary work outcomes will include: 1) temporary work cessation for any reason (i.e. sick leave, temporary WD, and short periods of unemployment lasting more than 2 months but less than 6 months); 2) occasional work absence (i.e. number of days missed from work per year); 3) reduction in usual amount of time worked (i.e. reduction in hours per week worked); 4) At-work productivity measured using a new scale currently being developed and validated based on a combination of the Workplace Activity Limitations Scale (WALS) and Work Limitations Questionnaire (WLQ); 5) Quality adjusted life year (QALY), will be measured using EQ-5D and SF-6D, 2 years post intervention, for the cost-utility analysis; 6) Changes from baseline in job satisfaction, self-efficacy at work, work-related risk factors for WD (job physical demand, job autonomy, difficulty commuting, self-employment and support from co-workers, employers and family), job accommodations, and job type will also be evaluated, as exploratory analyses, in an attempt to understand the effect of the intervention on mediators of work disability.

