We will also examine the incremental costs and benefits of receiving the intervention versus standard of care. Both a cost-effectiveness analysis and a cost-utility analysis will be performed. The outcome of our analysis will be the incremental cost-effectiveness ratio (ICER), which is the difference between the mean costs of providing competing interventions divided by the difference in effectiveness. Based on the primary outcome of the RCT, we will determine the incremental cost of the intervention per work cessation avoided relative to standard treatment. Because cost-effectiveness analyses are not robust to quantity or quality of life, we will also conduct a cost-utility analysis, where the primary outcome is the quality adjusted life year (QALY). Using health utilities measured by the EQ-5D and SF-6D, we will conduct a cost-utility analysis in which the incremental cost of the intervention relative to standard therapy per QALY gained will be determined. Important aspects of economic evaluations conducted alongside an RCT are excluding protocol driven costs, and dealing with missing data due to attrition. We will follow recommendations by the International Society for Pharmacoeconomics and Outcomes Research for missing cost and effectiveness data. We will use a combination of imputation and bootstrapping to quantify uncertainty due to missing values and finite study sample size. We will use propensity scores, stratified by treatment group, for imputing missing costs and effectiveness data due to attrition.

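### The QALY for the cost-utility analysis is set at 2 years, when program costs have been incurred but only the early part of the 5-year gain in time in work has accrued

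*Protocol article*

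**What the plan says.** The cost-utility analysis is the second of the trial's two objectives. Its effect measure is dated in the list of secondary outcomes: "Quality adjusted life year (QALY), will be measured using EQ-5D and SF-6D, 2 years post intervention, for the cost-utility analysis". No reason is given for choosing 2 years.

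Three other parts of the article bear on that choice.

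- **Data collection:** "Work outcomes, costs and quality of life will be assessed every 6 months, and other data once yearly". No end at year 2 is stated.
- **Outcome measures:** "The second primary outcome will be time to work cessation, measured over 5 years of follow up". The Limitations section calls 5 years the time needed to evaluate this outcome. It also says that preventing work disability will influence the decision to fund the program.
- **Sample size and analysis:** two economic analyses are described, one per QALY gained and one in which "we will determine the incremental cost of the intervention per work cessation avoided relative to standard treatment". Neither is given a time horizon there, and extrapolation beyond the observed data is not mentioned.

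**The concern.** The Intervention section describes a one-off program: five biweekly group sessions with modules in between, then occupational therapy and vocational consultations, each with a follow-up one month later. Essentially all of its cost falls well inside 2 years. The benefit that the Limitations and Discussion sections present as the reason to fund it, prevention of work disability, builds up more slowly. A person kept in work at month 20 has 4 months of extra work by year 2 and up to 40 months by year 5.

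A QALY is a quantity accumulated over time, so the stated time point works as a horizon. If the program keeps people in work, a horizon that closes at year 2 counts nearly all of its cost and only the start of that benefit. Controls are offered the program only at study end (Control group section), so the randomized comparison is planned to stay intact beyond year 2. The result at stake is the one meant to inform funders.

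**Working it through.** **Inputs**, all from Sample size and analysis:

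- Control rate: "a rate of work cessation of 12.77% per year in the control group", "based on the 40% work loss observed in controls over 4 years", "assuming an exponential distribution of time to work loss". As a hazard, −ln(0.60)/4 = 0.1277 per year.
- Effect: "to detect a 35% relative risk reduction (HR = 0.65) in the intervention vs. control group". Intervention hazard = 0.65 × 0.1277 = 0.0830 per year.

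**Reproducing the plan's own figure.** The Schoenfeld formula for HR 0.65, 80% power and two-sided alpha 0.05 gives 170 events. The 5-year event probabilities are 1 − exp(−0.1277 × 5) = 0.472 and 1 − exp(−0.0830 × 5) = 0.340, with mean 0.406. Then 170/0.406 ≈ 419, or 420 in two equal groups. With 20% loss, 210/0.80 = 262.5, so 263 per group and 526 in total. Both stated figures reproduce, so the model below matches the protocol's.

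**Gain in mean time in work to time T.** For hazard h, mean time in work to T is R(h,T) = (1 − exp(−hT))/h. The gain is R(0.0830,T) − R(0.1277,T).

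- T = 2: 1.843 − 1.765 = 0.078 years
- T = 5: 4.092 − 3.695 = 0.397 years
- Share accrued by year 2: 0.0778/0.3967 = 19.6%

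**If the effect stops at year 2** (assumption: equal hazards of 0.1277 afterwards). The difference in the proportion in work at year 2 is 0.8470 − 0.7746 = 0.0724. People kept in work go on accruing time, so the 5-year gain is 0.0778 + 0.0724 × R(0.1277,3) = 0.0778 + 0.0724 × 2.492 = 0.258 years. The share is 0.0778/0.258 = 30.1%.

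**If the effect lasts one year** (assumption). The gain during year 1 is 0.0208 years, and the difference in the proportion in work at year 1 is 0.0402.

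- By year 2: 0.0208 + 0.0402 × 0.939 = 0.0586 years
- By year 5: 0.0208 + 0.0402 × 3.132 = 0.1469 years
- Share: 39.9%

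**Other sensitivities of the 19.6%:**

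| Change | Share by year 2 |
|---|---|
| HR 0.58 (the cited trial's estimate) | 19.4% |
| HR 0.80 (assumption) | 20.0% |
| Discounting at 3% or 5% (assumption) | 20.7% or 21.5% |
| Window taken as 2.25 or 2.5 years from randomization (assumption) | 24% or 30% |

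**A different unit.** Counting cessations avoided rather than time in work gives 7.2 per 100 at year 2 and 13.2 per 100 at year 5, a share of 0.0724/0.1322 = 55%.

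**The case against.** The strongest reply is that the effect in the cost-utility analysis is the QALY from EQ-5D and SF-6D, not time in work. That is correct. Avoided work cessation is the effect in the separate cost-effectiveness analysis. Work loss reaches the cost-utility result only through productivity costs (WPAI-SHP, which includes work time missed) and any loss of utility on stopping work. Gains in productivity or coping among people still employed may also come early: the pilot reported favourable results at 12 months.

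Two years also fits parts of the design. At-work productivity is analysed then, and the trial may stop after the 2-year interim analysis (Study design section). Any longer horizon has to allow for that.

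Several stronger readings are tempting, and the documents do not support them.

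- *Only a fifth to a third of the QALY gain is captured.* The documents give no utility for work loss, so no QALY share can be computed. The range is also not a bound: it reaches 40% for a one-year effect, and 55% when cessations avoided are counted.
- *The cost-utility ratio is 3 to 5 times too high.* Those multiples come from 0.258/0.078 = 3.3 and 0.397/0.078 = 5.1. They describe program cost per working year gained, a ratio that the protocol does not plan. The planned ratio uses the difference in mean total costs.
- *The result is biased against the program.* A shorter horizon answers a different question. It understates value only if the benefit persists, which is the premise of the 5-year design but is not yet known.
- *The two economic analyses cover different periods.* The cost per cessation avoided is tied to the primary outcome, but no horizon is stated for it.
- *The data from years 3 to 5 will go unused.* The article does not say so. It dates the QALY outcome at 2 years and does not mention a longer analysis.

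An article may leave discounting and modelling detail to a fuller document. Here, however, the article does state a time point for the QALY, and that time point fits poorly with its own account of when the benefit arrives.

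**Conclusion.** The point holds as a weakness in a stated design choice. The QALY is fixed at 2 years without explanation, while 6-monthly utilities and costs are collected with no stated end and the work-cessation benefit is followed for 5 years. On the protocol's own hazard and HR, about 20% of the 5-year gain in time in work has accrued by year 2. That figure rests on exponential times and a constant HR; it becomes 30% or 40% if the effect lasts two years or one. It shows how slowly the work benefit builds up. It does not measure the error in the cost per QALY, whose size cannot be derived from the documents. The direction is conditional: if the benefit persists, the 2-year window tends to understate the program's value. Neither primary analysis is affected.

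**What to change.** In the secondary outcomes list and in the economic part of Sample size and analysis:

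1. Add a within-trial cost-utility analysis from randomization over the full randomized follow-up: 5 years, or to the stopping date if the trial ends at the 2-year interim. Use the 6-monthly EQ-5D, SF-6D and cost data, with costs and QALYs discounted.
2. Keep the 2-year result and label it an early analysis.
3. State the horizon of the cost per work cessation avoided, and use the same period for its costs and its effects.

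This is a change of wording and needs no new data collection. The price is more missing data in years 3 to 5 and a later final economic result. The imputation and bootstrapping already planned can handle the missing data, though the longer analysis will lean more heavily on the imputation assumptions.
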